### Other Measures

In addition to the primary and secondary outcomes, we will assess feasibility and acceptability outcomes, user data, in-game metrics, and diary recordings.

Feasibility and acceptability outcomes will include (1) cluster recruitment yield, defined as the proportion of clusters included relative to the total number of clusters invited, with a predefined success criterion of at least 80%; (2) uptake, defined as the proportion of participants who completed the minimum intervention dose (defined as completing baseline measurement and at least one game module) relative to all included participants, with a predefined success criterion of at least 66%; (3) engagement with the SMILE serious game based on in-game measures (Table 1); (4) adherence, operationalized as the average proportion of completed game modules relative to the total of 5 modules, with a predefined success criterion of at least 50%; (5) dropout, defined as the proportion of participants who disengaged from the study at any point between baseline and posttest relative to all participants, with a predefined criterion of less than 45%; (6) adverse events, assessed and summarized.

We will also collect user data restricted to the study apps (ie, the Game App and Companion App). User data will include app usage frequency; drop-off points (where users typically stop using the app); session duration; session start and end times; whether sessions are completed with or without interruptions; completion rates; frequency of engagement with the game; and the average time spent per session.

During SMILE gameplay, the Game App will collect various in-game metrics. These include measures of behaviors such as proximity to NPCs, performance in specific tasks, or in-game affect ratings. Table 1 provides a detailed description of these metrics.

As part of the intervention, in the SMILE Companion App, participants will be invited to complete brief weekly diary video recordings (approximately 3‐4 prompts) and longer recordings at baseline and posttest (approximately 8 prompts). Baseline and posttest prompts are general (eg, self-perception, mood and energy, coping, self-esteem, and potential anxiety or depression symptoms), while weekly prompts are tied to the current game module and ask participants to reflect on their experience. Recordings are encrypted and uploaded; audio and video streams are separated on the server and are not viewed or listened to by humans. Data remain encrypted until automated processing, and speech transcriptions are not stored. AI-based processing will extract exploratory digital markers previously linked in the literature [68-70] to anxiety and depression, including facial movement features (eg, action units, gaze, and head movement metrics) and acoustic or text-derived features (eg, energy and other signal parameters; counts of words and sentences and symptom-related terms), to examine associations with validated self-report outcomes and inform development of an explainable screening approach in young people.

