**Methods:**

SMILE uses a cluster-randomized, multisite, multiarm adaptive proof-of-concept design across 7 European countries, complemented by semistructured stakeholder interviews. Adolescents and young adults aged 10‐24 years are recruited mainly through schools, universities, and community channels; the target sample is 1438 participants. Clusters are assigned to 1 of 3 sequences comprising a neutral baseline period followed by 2, 4, or 5 game modules, and are randomized to a feedback or no-feedback version of the intervention. The intervention consists of the SMILE Game App (Nurogames and DigitalTwin Technology) and Companion App (RDIUP), which deliver CBT-based gamified content, self-monitoring, experience sampling, and, in one of the study conditions, automated personalized feedback. Primary outcomes are anxiety and depression. Secondary outcomes include well-being, resilience, emotion regulation, self-efficacy, and social anxiety. Feasibility, acceptability, engagement, app usage, in-game metrics, and diary-based digital markers are also assessed. Quantitative data will be analyzed using linear mixed-effects models with adaptive interim analyses. Qualitative stakeholder interviews with young people, their legal guardians, school professionals, and clinicians will be analyzed using inductive thematic analysis within a mixed-methods realist evaluation framework.

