### Study Design

#### Proof-of-Concept Study

The protocol follows the SPIRIT (Standard Protocol Items: Recommendations for Interventional Trials) guidelines [52], with the checklist available in Checklist 1.

This proof-of-concept study uses a cluster-randomized, multisite, multiarm adaptive trial design. Participants are grouped into clusters (see Participants Recruitment and Procedure), which are allocated to 1 of 3 sequences based on feasibility. Each cluster is subsequently randomized to either feedback or a no-feedback variant of the intervention. Clusters assigned to Sequence 1 complete a neutral baseline period with ESM, followed by Game Modules 1‐2. Clusters in Sequence 2 complete the baseline period and Game Modules 1‐4. Clusters assigned to Sequence 3 complete the baseline period and all 5 game modules (Figure 1).

The adaptive trial design is based on an initial site-level sample size calculated under the assumption that all steps in the sequence will be completed. Two stages of adaptive interim analyses will be conducted to estimate the effects of each intervention modality, including the control condition. Based on these interim results, sample sizes per cluster or site may be adjusted and decisions may be made to amend or discontinue specific intervention elements. Each adaptive interim analysis will estimate effects on the primary outcomes and identify key predictors of these effects. Sample sizes and randomization sequences may be updated accordingly. Additionally, active intervention elements may be modified based on model parameters, including patterns of feature use and the contribution of intervention-related indicators to interim effect sizes. The trial will be complemented by a process evaluation [53], using a mixed-methods realist evaluation approach. This design enables the assessment of multiple aspects of the proof-of-concept study (ie, acceptability, feasibility, reach, and efficacy). In particular, it supports the estimation of efficacy with a low risk of bias (eg, by minimizing contamination between experimental and control periods), while also allowing for in-depth process evaluation and enhancing the generalizability of findings in a naturalistic field setting.

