The intervention is rolled out over a 10-month period from September 2025 to June 2026. Three sequences are planned, separated by 3-week intervals; however, the length of the interval may vary depending on any implemented modifications. Clusters are allocated to sequences based on site-specific feasibility and readiness, meaning that clusters enter the rollout at different points depending on when they are prepared to initiate the intervention. Consequently, the number of clusters varies across sequences. In total, 46 clusters across 7 pilot sites will be included in the rollout. Each game module is designed to last no longer than 20 minutes. With 5 modules in total, including all study measures, participants are expected to spend a maximum of approximately 4.5 hours on the study, distributed over several weeks.

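### Adherence is scored out of 5 modules in every sequence although Sequences 1 and 2 offer only 2 and 4, so the meaning of the 50% criterion depends on the sequence mix

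*Protocol article*

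**What the plan says.** Other Measures lists six feasibility and acceptability outcomes. The fourth, adherence, is "the average proportion of completed game modules relative to the total of 5 modules, with a predefined success criterion of at least 50" per cent. The definition makes no exception by sequence.

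The Abstract (Methods) describes "sequences comprising a neutral baseline period followed by 2, 4, or 5 game modules". Study Design gives the detail:

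- Sequence 1: "Clusters assigned to Sequence 1 complete a neutral baseline period with ESM, followed by Game Modules" 1 and 2.
- Sequence 2: "Clusters in Sequence 2 complete the baseline period and Game Modules" 1 to 4.
- Sequence 3: "Clusters assigned to Sequence 3 complete the baseline period and all 5 game modules".

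On who goes where, Study Design states: "Clusters are allocated to sequences based on site-specific feasibility and readiness". It adds: "Consequently, the number of clusters varies across sequences". The number of clusters or participants in each sequence is not given.

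**The concern.** The denominator is the length of the full game, but most of the design does not offer the full game. A participant in Sequence 1 or 2 is marked down for modules that were never on offer. The score therefore combines two things: how much of the offered content people completed, and how much was offered. Only the first is adherence.

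Adherence belongs to the first primary objective, where the article counts it under reach, and it has a success threshold set in advance. Three consequences follow.

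- The threshold has no fixed meaning. How strict it is depends on the sequence mix, which is neither randomized nor fixed in advance.
- It can disagree with its neighbours. If everyone in Sequence 1 completed both modules and all measures, that group would score 100% on uptake (criterion at least 66%), 0% on dropout (criterion below 45%) and 40% on adherence.
- Scores from successive sequences are not comparable. The Data Analysis Plan foresees interim analyses at the end of each sequence and possible changes to the intervention in the light of engagement findings. If the adherence figure is read alongside these, a rise from one sequence to the next could be taken for improvement when it only reflects a longer game.

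**Working it through.** The 50% threshold is set, not derived, so there is no figure of the plan's own to reproduce. The check is what the threshold demands under the stated design.

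**Inputs.** Modules offered, m: 2, 4 and 5 in Sequences 1, 2 and 3 (Abstract; Study Design). Denominator 5 and threshold 0.50 (Other Measures). Participant shares w1, w2, w3: not in the document, so varied here as an assumption. The average is taken over participants.

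**Step 1: ceiling within each sequence**, m/5.

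- Sequence 1: 2/5 = 40%
- Sequence 2: 4/5 = 80%
- Sequence 3: 5/5 = 100%

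Share of offered modules needed to score 50%, which is 0.50/(m/5):

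- Sequence 1: 0.50/0.40 = 125%, not possible
- Sequence 2: 0.50/0.80 = 62.5%
- Sequence 3: 0.50/1.00 = 50%

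**Step 2: pooled ceiling and effective demand.** Ceiling = 0.4·w1 + 0.8·w2 + 1.0·w3. Demand = 0.50/ceiling, the share of all offered modules that must be completed.

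| Assumed shares, Sequences 1/2/3 | Ceiling | Demand |
|---|---|---|
| 10/20/70 | 0.04 + 0.16 + 0.70 = 90% | 55.6% |
| 25/25/50 | 0.10 + 0.20 + 0.50 = 80% | 62.5% |
| Equal thirds | (0.4 + 0.8 + 1.0)/3 = 73.3% | 68.2% |
| 50/25/25 | 0.20 + 0.20 + 0.25 = 65% | 76.9% |
| 80/10/10 | 0.32 + 0.08 + 0.10 = 50% | 100% |

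**Step 3: same behaviour, different result.** Suppose participants in every sequence complete 60% of what they are offered. The pooled score is 0.6 × ceiling:

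- 10/20/70: 0.6 × 0.90 = 54%, pass
- Equal thirds: 0.6 × 0.733 = 44%, fail
- 50/25/25: 0.6 × 0.65 = 39%, fail

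By sequence, the same constant 60% appears as 0.6 × 0.4 = 24%, then 0.6 × 0.8 = 48%, then 60%: a steep rise with no change in behaviour.

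**Step 4: when the pooled criterion becomes impossible.** The ceiling must fall below 50%.

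- All others in Sequence 2: 0.4·w1 + 0.8·(1 − w1) < 0.5, so w1 > 0.3/0.4 = 75%
- All others in Sequence 3: 0.4·w1 + 1.0·(1 − w1) < 0.5, so w1 > 0.5/0.6 = 83.3%

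**Step 5: with modules offered as denominator.** The ceiling is 100% in every sequence and for every mix. The 50% criterion then means, on average, 1 of 2, 2 of 4 or 2.5 of 5 modules.

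**The case against.** The strongest reply is that the criterion applies to an average and the article does not say that it is judged by sequence. Read as one pooled figure, it can be met: full completion passes unless Sequence 1 holds more than about 75% to 83% of participants. This stands. A reader might infer that the criterion is unreachable, or that each fully compliant Sequence 1 participant fails it. The document supports neither. What remains is that the pooled bar is above 50% of offered modules whenever anyone is in Sequence 1 or 2, by an amount that the mix decides.

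A reader might also infer that missing 50% would block a definitive trial. The article sets a success criterion but attaches no decision to it. Adherence is one of several feasibility measures, and the findings are only said to inform a later trial.

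Dividing by 5 could be defended as the dose received of the complete programme, which the article describes as five modules. That is a sensible quantity, but the article calls the measure adherence and gives no such reason. This softens the point without answering it.

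Finally, the Results section reports two sequences complete, so a new denominator loosens a preset criterion after data have accrued. This is a fair caution, and it shapes the fix.

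Deferring the matter to the analysis plan does not remove it. The article states numerator, denominator and threshold, and the denominator does not fit the design in the same article.

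**Conclusion.** The point holds as a should-fix. The ceilings of 40%, 80% and 100% follow directly from the article and need no assumption. Sequence 1 data taken alone cannot reach 50%, and the pooled score mixes adherence with the number of modules offered.

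The size of the pooled effect cannot be fixed from the document because the split over sequences is not given. Over the assumed mixes 10/20/70, equal thirds and 50/25/25, the nominal 50% amounts to about 56%, 68% and 77% of offered modules.

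The error is confined to a feasibility measure. The mixed models for anxiety, depression and the secondary outcomes do not use this score, the minimum-dose analysis sample rests on completing at least one module, and the sample size does not depend on it. Nothing here supports a claim that the efficacy results are compromised.

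**What to change.** Define adherence as modules completed divided by modules offered in the participant's assigned sequence (2, 4 or 5). Apply the 50% criterion to the average of that proportion, and report it by sequence as well as overall, with the number of participants in each sequence.

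Because two sequences are already complete, record this as a protocol change and disclose it with the results, as Ethical Considerations promises for any change. Keep reporting the out-of-5 figure beside it, labelled as dose received of the full programme, so that readers can see the result under both definitions.

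The cost is a revised definition, a note of the change and one extra line in the feasibility table. Module completion is already collected. There are two small downsides. The criterion becomes easier to meet than the one set in advance, which is why both figures are needed. And in Sequence 1, completing 1 of 2 modules scores 50%, which is the same gameplay as the minimum dose used for uptake, so the criterion adds little there beyond uptake. Reporting by sequence makes this visible.

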### Sample

#### Proof-of-Concept Study

The trial will be conducted among clusters of adolescents and young adults, aged 10 to 24 years who fulfill the inclusion criteria. The sample size calculation was specified a priori assuming 3 sequences with 4 clusters per sequence. Because the sample size calculation, conducted with the Shiny CRT Calculator [54], permitted specification of only a single intervention condition, the sample size estimate was doubled to reflect the trial’s intervention structure. The calculation assumed an error level of α=.05, power of 1–β=0.80. Clustering was modeled with an intracluster correlation (ICC) of 0.01 [55,56], and within-participant autocorrelation was set to 0.60 [57]. A standardized effect size of 0.20 was assumed for all primary outcomes. Since the sample is considered to derive from a healthy population, changes in depression and anxiety symptoms were expected to be small. Applying the same effect size across outcomes provided a consistent basis for sample size estimation and represented the smallest effect of interest. Given the exploratory nature of the study, no formal alpha adjustment was applied. A dropout rate of 50% was assumed. Under these assumptions, 24 participants per arm per site are required, corresponding to 992 participants overall. On top of the included dropout expectations, to account for attrition reported in comparable trials (24%‐83%) [58,59], the recruitment target was increased to 1438 participants.

Because the trial follows an adaptive design with 2 interim analyses, the initial sample size estimate will be treated as provisional. Interim data will be used to update key parameters and adjust sample size for subsequent stages as needed. This approach will enable us to gather sufficient data to inform potential subsequent definitive randomized controlled trials and to refine the intervention as necessary.

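### The single <45% dropout criterion pools sequences of 2, 4 and 5 modules, so it is not the dropout of the five-module game and can be met when that is 50% or somewhat more.

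*Protocol article*

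**What the plan says.** Dropout is the fifth feasibility outcome in the protocol article, section Other Measures: "dropout, defined as the proportion of participants who disengaged from the study at any point between baseline and posttest relative to all participants". The threshold is a single value, below 45%. Numerator, denominator and threshold are all fixed there, with no split by sequence.

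The abstract describes "a neutral baseline period followed by 2, 4, or 5 game modules". The Study Design section adds that "Clusters assigned to Sequence 3 complete the baseline period and all 5 game modules"; Sequence 1 ends after Module 2 and Sequence 2 after Module 4. The section on measures places posttest (T3) after the intervention is completed.

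The sequences are not filled by randomisation: "Clusters are allocated to sequences based on site-specific feasibility and readiness". The same section continues: "Consequently, the number of clusters varies across sequences". The total is given ("In total, 46 clusters across 7 pilot sites will be included in the rollout"), but not the number of clusters or participants in each sequence.

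The sample size section states: "A dropout rate of 50% was assumed". It gives no time horizon for that figure and does not link it to a sequence.

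**The concern.** A Sequence 1 participant can drop out only during the baseline period and two modules. A Sequence 3 participant can drop out during the baseline period and five. Both count equally towards one proportion and one threshold. The pooled result is thus a weighted average of three different quantities, with weights that depend on which clusters were ready when. It does not estimate retention for any one version of the programme, and if dropout accumulates over modules it lies below the five-module figure.

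Feasibility is part of the first stated objective, and the findings are meant to inform a definitive trial. A pooled result below 45% could be read there as adequate retention for the whole game, which only Sequence 3 delivers.

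**Working it through.** The 45% threshold is a chosen value, so there is no calculation of the plan's to reproduce. The check asks what pooled dropout results from a given Sequence 3 dropout.

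**Inputs from the protocol article:** 2, 4 and 5 modules; threshold 45%.

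**Assumptions, because the article gives no figures:** the share of participants w in each sequence; the pattern of loss over time; Sequence 3 dropout of 50% as an illustrative value.

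**Formula.** With constant retention r per step and m steps, dropout is d = 1 − r^m, and pooled dropout is w1·d1 + w2·d2 + w3·d3.

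**Steps = modules (2, 4, 5).** r = 0.5^(1/5) = 0.871.
- d1 = 1 − r² = 24.2%; d2 = 1 − r⁴ = 42.6%; d3 = 50%.
- Equal thirds: (24.2 + 42.6 + 50)/3 = 38.9%, below 45%.

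**Baseline period as one more step (3, 5, 6).** r = 0.5^(1/6) = 0.891.
- d1 = 29.3%; d2 = 43.9%; d3 = 50%.
- Equal thirds: (29.3 + 43.9 + 50)/3 = 41.1%, below 45%.

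**Other splits.** In each cell, the first value is for modules only and the second for the baseline as a step. The last column is the Sequence 3 dropout at which the pooled figure reaches 45%.

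| Split, Sequences 1/2/3 | Pooled dropout if Sequence 3 = 50% | Sequence 3 dropout at pooled 45% |
|---|---|---|
| Equal thirds | 38.9% / 41.1% | 57.1% / 54.4% |
| 50/30/20 | 34.9% / 37.8% | 62.5% / 58.4% |
| 25/25/50 | 41.7% / 43.3% | 53.7% / 51.9% |
| 20/20/60 | 43.4% / 44.6% | 51.8% / 50.4% |
| 10/20/70 | 45.9% / 46.7% | 49.0% / 48.2% |
| 10/10/80 | 46.7% / 47.3% | 48.2% / 47.6% |

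**Limit on the Sequence 3 share.** Let Sequences 1 and 2 be equal in size and solve s·50 + (1 − s)·(mean of d1 and d2) = 45.
- Modules only: mean 33.4%, s = (45 − 33.4)/(50 − 33.4) = about 70%.
- Baseline as a step: mean 36.6%, s = (45 − 36.6)/(50 − 36.6) = about 63%.

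Above these shares, 50% in Sequence 3 no longer passes.

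**Early loss common to all sequences.** Let a fraction f leave before Module 1, with constant loss per module afterwards, equal thirds and Sequence 3 at 50%. Pooled dropout is 40.9% for f = 10%, 42.9% for 20%, 45.1% for 30% and 47.5% for 40%. Masking ends at about 30%.

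**Without an assumption on the pattern of loss.** With equal thirds and Sequence 3 at 50%, the criterion is met whenever Sequences 1 and 2 average less than (0.45 − 0.5/3)/(2/3) = 42.5%.

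**The case against.** The strongest objection is that the size rests on a pattern of loss and a split that the article does not give. Early loss is also not remote. The article's own uptake criterion of at least 66% tolerates 34% who do not complete baseline and one module. With 34% early loss, equal thirds and Sequence 3 at 50%, pooled dropout is 44.9% if the loss occurs through Module 1 and 46.0% if it occurs before Module 1. That is at or above the threshold, with essentially no masking. This stands and limits the claim to what can happen.

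It can also be said that dropout is defined as leaving the study, so the pooled figure is a coherent measure of retention in the trial as run. That stands too, and is why the figure should be kept.

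The article further collects drop-off points and completion rates, scores adherence against all five modules, and plans interim analyses after each sequence. None of these is tied to the 45% criterion. The adherence rule in fact shows the mismatch: a Sequence 1 completer reaches at most 2/5 = 40% on adherence, yet counts as fully retained under the dropout rule. A statistical analysis plan that is not shown may report dropout by sequence, but the criterion fixed in this article is pooled.

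Four stronger readings might be inferred and are not supported:
- **A go/no-go rule.** The article gives a predefined criterion and attaches no consequence to missing it.
- **The planning 50% as five-module dropout.** The sample size section does not say this. Read as overall dropout, 50% simply fails the criterion and nothing is hidden.
- **Fixed posttest weeks per sequence.** These can only be guessed from the headings of Table 2; the module-based calculation does not need them.
- **The five-module game as the settled product for the next trial.** The article allows modules and other elements to be changed.

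**Conclusion.** The point holds in a limited form. The pooled proportion is not the dropout of the five-module game, and this follows from the definition and the design without any calculation. It can fall below 45% when five-module dropout is 50% or somewhat more. With constant loss per module and equal sequence sizes, 50% becomes 39% (41% with the baseline as a step), and the criterion is met up to about 54-57%. The bound is higher if few participants are in Sequence 3. Masking of a 50% loss disappears if Sequence 3 holds roughly 63-70% or more of participants, or if about 30% or more leave before the sequences diverge. The documents do not show which case applies, so the finding is that the criterion can mislead about the full programme, not that it will.

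**What to change.** Keep reporting the pooled proportion against <45% as predefined. Add two things:

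1. Report dropout separately for Sequences 1, 2 and 3, with the number of participants in each.
2. Base any statement that retention in the full programme meets <45% on dropout through Module 5, estimated in Sequence 3. As a sensitivity analysis, give a Kaplan-Meier estimate through Module 5 that censors Sequence 1 and 2 participants at their planned end.

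Two sequences were complete by March 2026, so this should be reported openly as a clarification and not as a replacement of the criterion.

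The cost is a few sentences, and the data are already collected. The Sequence 3 estimate has a smaller denominator, a wider interval and probably a less favourable value. Because sequences are filled by readiness and the game may change between them, differences between sequences are descriptive only, and the Kaplan-Meier estimate carries the same reservation.
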